### Group allocation (minimisation)

After completion of the screening visit (CPET), patients who fulfil the inclusion criteria are randomised using computer-generated random numbers, into either intervention or control group. For group allocation, a probabilistic minimisation procedure is used to achieve balanced groups in regard to parameters known to be relevant for outcome after major surgery. We have included the following parameters in the minimisation algorithm (SecuTrial, V.6.1.1.10): type of surgery (visceral, urologic, cardiovascular, orthopaedic, thoracic), smoking, presence of anaemia (haemoglobin below 120 g/L in females, <130 g/L in males), nutritional deficit (NRS ≥3), age group (65–74, 75–84, 85+), ischaemic heart disease or heart failure, known diabetes, sex, obesity (body mass index (BMI) >30 kg/m^2^) and use of extracorporeal circulation.

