## Methods

### Study design

This is a national multicentre, multidisciplinary, prospective, two-arm parallel-group, randomised, controlled superiority trial with blinded outcome assessment. We aim to include 466 patients within 3 years. The present protocol complies with the Standard Protocol Items: Recommendations for Interventional Trials (SPIRIT) 2013 guidelines, defining standard protocol items for clinical trials.

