### Perioperative management

Perioperative management follows the usual care of the corresponding clinic, usually following standardised, multielement ERAS guidelines. Management decisions such as extension of monitoring and admission to postoperative care (postoperative care unit vs intermediate or intensive care unit (ICU)) are purely based on clinical judgement, taking the results of the preoperative testing into account as it is accessible by the clinicians through the electronic healthcare record system.

In case of raised preoperative NTproBNP >200 pg/mL, hsTroponinT will be measured 6 hours after surgery as well as on the first and second postoperative day.^81^

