### Statistical analysis

Data will be analysed on an intention-to-treat basis (primary outcome). Primary and secondary outcomes for the intervention and control groups will be compared.

Primary outcome: We expect that CCI will be skewed, so we will describe CCI as the median plus first and third quartiles. To test the hypothesis (H0) that the study arms result in similar CCIs (in other words, prehabilitation does not prevent postoperative complications), we will use a generalised linear model that can account for skewed data and zero inflation. The model will be adjusted for the minimisation factors used at randomisation. If no adequate model can be fit, the non-parametric Mann-Whitney U test will be used.

Secondary outcomes: All secondary outcomes will be described as means plus SD or median plus first and third quartiles for continuous data as appropriate. Categorical parameters will be described as frequencies plus percentage per time point. To account for repeat measurements of patients, we will use generalised linear mixed models to test the hypothesis of both study arms being equal in terms of secondary outcomes over time. Models will be adjusted for minimisation factors as well as baseline values (before randomisation) of the respective outcome.

Data distribution will be assessed by visual inspection of Q-Q plots.

As a secondary analysis, we will perform a PP analysis. Since the time between randomisation and surgery might differ between the two randomisation groups, we will additionally adjust generalised linear models of the primary outcome for this factor in a sensitivity analysis. Further, we will analyse the impact of adherence to the interventions to the primary outcome.

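### Centre enters neither the minimisation nor the stated primary analysis of this multicentre trial: a modest, avoidable loss of precision, not a bias

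*Protocol article*

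**What the plan says.** Under Study design, the Protocol article states: "This is a national multicentre, multidisciplinary, prospective, two-arm parallel-group, randomised, controlled superiority trial". Neither the number of centres nor their expected size is given.

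Under Group allocation (minimisation), "a probabilistic minimisation procedure is used to achieve balanced groups in regard to parameters known to be relevant for outcome after major surgery". The list of factors begins "We have included the following parameters in the minimisation algorithm (SecuTrial, V.6.1.1.10): type of surgery" and closes with "and use of extracorporeal circulation". It holds ten factors: type of surgery, smoking, anaemia, nutritional deficit, age group, ischaemic heart disease or heart failure, diabetes, sex, obesity and extracorporeal circulation. No stratification by centre is described.

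Under Statistical analysis, the primary model is a generalised linear model for skewed, zero-inflated data: "The model will be adjusted for the minimisation factors used at randomisation". Then: "If no adequate model can be fit, the non-parametric Mann-Whitney U test will be used". The secondary models add the baseline value of the outcome, and the sensitivity analysis adds the time from randomisation to surgery. Centre appears in none of these.

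Under Perioperative management, "Perioperative management follows the usual care of the corresponding clinic"; the same sentence adds that this care usually follows standardised enhanced-recovery (ERAS) guidelines.

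**The concern.** The minimisation is meant to balance what is known to matter for outcome, and the analysis then conditions on the same factors. Centre is a usual member of that set in a multicentre surgical trial, because usual care and decisions on monitoring and intensive care are made locally. If CCI differs between centres after allowing for the ten factors, two things follow from the plan as written. The extra variation sits in the error term and widens the confidence interval for the treatment effect. And nothing in the allocation keeps the arms balanced within a centre, which leaves centre-specific summaries in small centres open to chance imbalance. At stake is some precision that could be had without recruiting more patients.

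**Working it through.** **Inputs from the Protocol article (Sample size).** 388 analysable patients, alpha 0.05, power 0.80, Wilcoxon-Mann-Whitney test. Sidedness is not stated; two-sided is assumed. The planning CCI (median 30, IQR 21 to 37) comes from one hospital.

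**Inputs assumed.** R², the share of CCI variance left after the ten factors that centre explains: 0.01 to 0.10. Number of centres: 3, 6 or 10. Centre sizes: 20 to 233 patients. None of these is in the document.

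**The plan's own figure.** A normal shift of 4.5 points (15% of 30) with SD 16/1.349 = 11.86 gives totals of 220 to 256, depending on the Wilcoxon correction, so 388 is not reproduced. The CCI distribution used is not stated, so this does not show 388 to be wrong. The check below takes 80% power at 388 as given and asks only what centre would change.

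**Step 1: gain from adjusting for centre.** At 80% power the standardised signal is 1.96 + 0.8416 = 2.8016. Removing a share R² of the residual variance divides it by √(1−R²):

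power = Φ(2.8016/√(1−R²) − 1.96); equivalent extra patients = 388/(1−R²) − 388, rounded up.

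| R² (assumed) | Power with centre term | Equivalent extra patients |
|---|---|---|
| 0 | 80.0% | 0 |
| 0.01 | 80.4% | 4 |
| 0.02 | 80.8% | 8 |
| 0.05 | 82.0% | 21 |
| 0.10 | 84.0% | 44 |

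**Step 2: the other reading of the planning spread.** A single hospital's data hold no between-centre component. If 80% power is taken to rest on a within-centre spread, omitting centre gives Φ(2.8016·√(1−R²) − 1.96): 79.6% at 0.01, 79.2% at 0.02, 78.0% at 0.05 and 75.7% at 0.10. The difference is of the same order as in Step 1, seen from the other side.

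**Step 3: validity.** Simulation with 388 individually randomised patients, a normal outcome, 3, 6 or 10 equal centres, centre shares of 0.02, 0.05 and 0.10, and 3,000 runs per setting. Without a centre term the type I error was 4.8% to 5.7%. The simulation standard error is √(0.05·0.95/3000) = 0.4 points, so this is compatible with 5%. At a share of 0.10, power without the centre term was 82.0%, 79.3% and 80.2% (3, 6 and 10 centres), against 84.4%, 82.7% and 83.2% with it: 2 to 3 points. At 0.02 and 0.05 the difference was about 1 point or less.

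**Step 4: balance within a centre.** Treating allocation within a centre as simple 1:1, the chance of a 60:40 split or worse is 50% in a centre of 20, 27% in one of 40, 15.5% in one of 60, 6% in one of 100 and 0.3% in one of 233.

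**The case against.** Four objections deserve weight.

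*The ten factors may already carry much of what centre would.* Type of surgery and extracorporeal circulation are both minimised and modelled. The word clinic under Perioperative management may mean a surgical department rather than a hospital, and care is said usually to follow common guidelines. This stands as a reason to expect a small remaining centre effect, which is why the range starts at 1%. It does not cover differences between hospitals within one specialty.

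*The unseen statistical analysis plan could add a centre term.* The article does not say that the minimisation factors are the only covariates. This stands for the model. It does not stand for the allocation, where the factor list is closed and has been in use since the first patient.

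*A centre term is not free.* The model already carries ten factors and may have two parts. A fit that fails sends the analysis to the unadjusted test and loses all adjustment. This stands as a small risk, and it is a reason to make the fallback centre-stratified.

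*The calculation is approximate.* It uses a normal approximation, whereas CCI is expected to be skewed and zero-inflated. This stands; the figures show order of magnitude only.

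A reader might infer more than the document supports. Chance imbalance within small centres could be read as centre being confounded with treatment; under individual randomisation it is not, and the simulation shows no inflation of the type I error. One might also suppose that the primary endpoint is scored differently at each centre; the article assigns it to one independent, blinded committee of three experts. Finally, one might start from the 373 patients left after 20% dropout from 466 and blame the lower power on centre; that shortfall comes from how dropout was added and is a separate matter.

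**Conclusion.** The point holds as a cheap improvement in precision. The article fixes an allocation list without centre, ties the primary model to that list, and falls back on an unadjusted test. At 388 analysable patients, accounting for centre would move power from 80% to about 80.4% if centre explains 1% of the remaining variance, and to about 84% if it explains 10%, equivalent to roughly 4 to 44 patients. The size rests on an assumed centre variance, a two-sided 5% test and a normal approximation; with neither the number of centres nor their variance stated, it cannot be narrowed. Within-centre imbalance is likely in small centres, but it mainly affects centre-level description. The treatment comparison stays valid without the change.

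**What to change.** 1. Add centre to the primary and secondary models, as a random intercept or as a fixed effect with small centres pooled by a rule set blind to outcome.
2. Replace the unadjusted Mann-Whitney fallback with a van Elteren test stratified by centre, using the same pooling rule.
3. Preferably, add centre to the probabilistic minimisation for patients still to be randomised. The article reports 18 patients included by October 2022 out of 466 planned, so at that stage nearly all of the sample would have benefited.
4. If the randomisation system or the analysis plan already handles centre, say so under Group allocation and Statistical analysis.

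The cost is an amendment, a configuration change in the randomisation system and one more term per model. There are three downsides: slightly looser balance on the other ten factors, somewhat greater predictability of allocation within small centres of an unblinded trial (the random element in the minimisation limits this), and a small added risk that a complex zero-inflated model does not fit. If item 3 is judged not worth the predictability, items 1 and 2 still recover most of the precision.

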### Patient and public involvement

Patients or the public were not involved in the design, or conduct, or reporting, or dissemination plans of our research.

### Study interventions

#### Control group

For the control group, there is a medical work up by the study team of the results obtained. In case of abnormalities found mandating medical interventions prior to surgery based on clinical judgement, these will be initiated either by the research team or the general practitioner (GP) at the patients' discretion. Regardless of existing deficits, the patient’s GP will be informed about the patient’s study participation and will receive the results of the screening assessment. All study patients wear the accelerometer between screening and preoperative visit.

#### Intervention group

For patients of the intervention group, we will implement an individually tailored, multimodal prehabilitation programme consisting of physical and respiratory training, correction of nutritional deficits and anaemia and smoking cessation counselling based on the identified deficits.

##### Physical activity

All patients perform a tailored exercise intervention based on their individual physical fitness level. The intervention includes 1–2 sessions (60 min each) with a licensed physical therapist trained in exercise prescription and 5 years of experience in the field of exercise prescription. The physical therapist will assess the patient’s physical abilities and discuss the possibilities of incorporating at least 30 min of exercise at least five times per week at home. Based on the planned surgical intervention (e.g., hip, back), the preferences and barriers of each individual patient, the physical therapist composes a tailored personal training programme. This physical training programme is composed of endurance training (e.g., walking at moderate intensity, climbing stairs), resistance training (e.g., upper limb strengthening using a resistance band, Theraband, Akron, Ohio, USA) and inspiratory muscle training (Threshold IMT, Philips Healthcare, Horgen, Switzerland). The patient receives the personal training programme either via smartphone application or as a hard copy. The non-supervised home-based exercise training sessions will be supported by illustrative materials (smartphone application with pictures and videos or brochure with pictures). Each patient receives weekly phone calls by the physical therapist to record adherence, as a motivational strategy, to discuss any boundaries to adhering to the programme and to progress the exercises if possible. An exercise intervention might look like the following programme: Respiratory: Inspiratory muscle training (IMT) at 40% of measured maximum inspiratory pressure (MIP), 60 repetitions daily (30 morning, 30 evening); Endurance: outdoor walking at moderate intensity, 30 min 5 days/week; strength: squats with bedside support, 3×10 repetitions, as deep as pain free, 5 days/week.

##### Nutritional support and management of anaemia

We aim to optimise the nutritional status to minimise the surgery-related catabolic stress. Nutritional risk will be assessed at baseline, preoperatively and postoperatively during study visits using the NRS-2002 total score.^73^ This validated screening tool attributes scores of different levels of nutritional status to patients based on weight loss, BMI and food intake, taking into account disease severity (degree of stress metabolism) and age. NRS-2002 total score is obtained by adding impaired nutritional status score (0–3 points), severity of disease score (0–3 points) and age (1 point if age ≥70 years). Patients are classified as being at high nutritional risk or malnourished (score ≥3) or at low risk (score <3), according to the total score obtained (see figure 2).

**Figure 2 F2:**
[figure not shown]
Nutrition and diabetes intervention workflow. NRS-2002, Nutrition Risk Screening 2002; PG-SGA, The Scored Patient Generated Subjective Global Assessment; 25-OH-D, 25-hydroxy-vitamin D; RBC-Folate, Erythrocyte Folate; Hb, Haemoglobin; eGFR, estimated Glomerular Filtration Rate; EPO, erythropoietin; HbA1c, glycated haemoglobin; HBE, Harris-Benedict Equation; PAL, Physical Activity Level; BW, bodyweight; ON, Oral Nutrition; ONS, Oral Nutritional Supplements; EN, Enteral Nutrition. * Usage of adjusted bodyweight, if BMI>25.

After screening with NRS-2002, nutritional status will be further quantified according to the patient generated SGA (PG-SGA) score, which defines the need for nutritional intervention: no intervention needed (score 0–1), needing education by a professional (score 2–3), requiring intervention by a certified dietitian (score 4–8) and having a critical need for symptom management and/or nutrient intervention (score ≥9).^74^

Patients with low risk for malnutrition (NRS-2002 <3) will be provided with dietary advice on how to achieve set individual nutritional targets (energy intake according to the Harris-Benedict equation and protein intake of >1 g/kg BW/day). Adjusted bodyweight will be used in case of BMI >25 to prevent overestimation of nutritional requirements.

Patients at high risk for being malnourished (NRS-2002 ≥3, PG-SGA ≥4) will receive dietary counselling and individualised plans to meet their energy and protein requirements. Individual energy needs will be calculated using the Harris-Benedict equation. A protein intake of 1.2–1.5 g/kg BW will be recommended to all malnourished participants (using adjusted body weight when BMI >25, as described above). To facilitate the achievement of these goals, oral nutritional supplements will be prescribed. The aim is to achieve at least 75% of the set energy and protein goal. The adherence in the malnourished group will be checked by performing 24 hours dietary recall 3 days after baseline visit. In case of reaching <75% of set dietary goals, the intervention will be escalated to enteral nutrition. If the goals are not fulfilled during the following 3 days as evaluated with 24 hours dietary recall, the intervention will be escalated to parenteral nutrition.

If scheduled for major abdominal surgery and if indication exists according to Swiss Society for Clinical Nutrition, patients will additionally receive immunonutrition (e.g., high protein oral supplements enriched with immunonutrients such as arginine, omega-3-fatty acids and nucleotides) for five consecutive days before surgery,^75 76^ as per ERAS guidelines. All participants will receive two doses of carbohydrate loading, one dose on the evening before and one up to 2 hours prior to surgery.^76^

In patients with an established or newly diagnosed diabetes and HbA1c >7.5%, glucose levels will be optimised using pre-scribed glucose monitoring and treatment intensification where appropriate. Delivered strategies represent best practice of diabetes care based on the European Association for the Study of Diabetes (EASD)/American Diabetes Association (ADA) position statement.^77^

Independent of the nutritional status, individual deficits in vitamin D, iron, vitamin B_12_ and folate will be addressed. Vitamin D is associated with muscle mass and muscle strength. Additionally, hypovitaminosis D was found to be correlated with increased risk of postoperative complications.^78 79^ It will be supplemented daily according to the blood sample values: 1000 U/day for patients with vitamin D deficiency (25-hydroxy-vitamin D <50 nmol/L) and a one-off substitution of 150 000 U for patients with severe vitamin D deficiency (25-hydroxy-vitamin D <25 nmol/L).^80^

In case of severe renal anaemia (haemoglobin <100 g/L, estimated glomerular filtration rate <45 mL/min/1.73 m^2^ and a reticulocyte index below 2), a one-off erythropoietin application (Mircera, Vifor Pharma, Switzerland) will be provided.

##### Smoking cessation

The smoking cessation programme includes intensive counselling by a graduate psychology student during three phone-call sessions as well as dispensary of nicotine replacement therapy (NRT) perioperatively if desired by the patient. NRT consists of transdermal application for moderate to heavy smokers and individual supplementation with chewing gum or lozenges (Nicotinell, GlaxoSmithKline, Brentford, UK) according to the current guidelines. NRT will either be handed out during the nutritional intervention session or sent via postal mail. The goal is to achieve a reduction in smoking quantity (cigarettes per day) of 80% before surgery.

##### Compliance with the study interventions

Adherence rates to the physical fitness intervention are primarily collected by patient-recorded standardised physical activity log books, by weekly phone calls and complemented by accelerometer data (AX3, Axivity, Newcastle, UK). Successful completion of the exercise programme is defined as adherence to 80% of prescribed exercise sessions.

For patients with an NRS-2002 ≥3 or PG-SGA ≥4, weekly phone calls by the dietician will secure adherence to the study intervention. In addition, the patients will document the intake of prescribed supplements in a log book.

The three phone call smoking cessation counselling sessions for smokers are intended to monitor and further adherence to smoking cessation. Further, exhaled CO is measured at every visit.

Reasons for non-compliance are recorded during all phone calls and strategies to increase compliance are sought in the discussion with the patient.

### Perioperative management

Perioperative management follows the usual care of the corresponding clinic, usually following standardised, multielement ERAS guidelines. Management decisions such as extension of monitoring and admission to postoperative care (postoperative care unit vs intermediate or intensive care unit (ICU)) are purely based on clinical judgement, taking the results of the preoperative testing into account as it is accessible by the clinicians through the electronic healthcare record system.

In case of raised preoperative NTproBNP >200 pg/mL, hsTroponinT will be measured 6 hours after surgery as well as on the first and second postoperative day.^81^

### Postoperative assessment

The postoperative assessment as described above will be repeated at 30 days after surgery when the patient is scheduled for surgical follow-up. The only difference from the preoperative assessment is that micronutrient and iron status are not measured again.

### Blinding procedure

This is an unblinded study due to the nature of the intervention. Nevertheless, the treating anaesthetist, while having access to the results of the preoperative assessment results via EHR, is blinded to group allocation. Primary end point adjudication committee will also be blinded (see below).

### Data collection

All data will be collected by the research team and documented in a research database (RedCap) according to local legislation. Data will be verified by dedicated members of the research team. Original source data is available in the EHR or in patients’ files.

### End point adjudication Committee

In order to standardise the review process and to reduce bias and variability in assessing the primary outcome, the CCI at 30 days will be assessed by an independent and blinded committee of three experts, which are otherwise not involved in the trial. The experts are yet to be nominated.

### Data monitoring

The data will be monitored by an external institution (Clinical Trials Unit, University of Bern) at regular intervals according to a preset monitoring plan to ensure the safety of the trial participants and the integrity of the trial data.

